## Abstract

**Background:**

Post-stroke cognitive impairment (PSCI) is a series of syndromes that meet the diagnostic criteria for cognitive impairment that appear after a stroke. The treatment of PSCI with oral drugs alone is not ideal and has obvious side effects. Therefore, complementary and alternative treatments are needed for patients with insufficient or significant side effects of oral medications. Therefore, we will evaluate the clinical effectiveness and safety of acupuncture in the treatment of PSCI.

**Methods/design:**

In this study, patients will be randomly divided into two groups. Intervention group: acupuncture combined with oral medication. Control group: Western medicine treatment plan. All participants will continue to receive conventional drug treatment. The selection of outcomes will be evaluated by Mini Mental State Examination Scale (MMSE) at week 12. The scale will be conducted by two well-trained reviewers who will conduct joint MMSE inspections on participants. The test time will be selected 3 days before treatment and once 4 weeks after treatment. After the MMSE test, the two raters scored independently, and the average of the two was used as the final score.

**Discussion:**

This trial may provide evidence regarding the clinical effectiveness, safety, and cost-effectiveness of acupuncture for patients with PSCI.

**Trial registration:**

ClinicalTrials.gov ChiCTR2000029926. Registered on 17 February 2020 http://www.chictr.org.cn/showproj.aspx?proj=49356

## Background

Cognitive function is composed of multiple cognitive areas such as memory, computing power, time orientation, space orientation, structural ability, execution ability, language understanding ability, and expression application ability [1]. Cognitive impairment refers to a series of syndromes with varying degrees of cognitive impairment from mild cognitive impairment to dementia caused by various reasons. These behavioral and emotional disorders have become important diseases affecting the health and quality of life of middle-aged and elderly people, as well as important causes of disability for patients [2]. The disease places a heavy burden of care and economic burden on society and families. Stroke can cause multiple types and varying degrees of cognitive dysfunction. The definition of post-stroke cognitive impairment (PSCI) was also clarified in “the 2016 Chinese Expert Consensus on Post-Stroke Cognitive Impairment Management”. It points out that PSCI is a series of syndromes that meet the diagnostic criteria for cognitive impairment that appear after a stroke [3, 4]. It highlights the potential causal relationship between stroke and cognitive impairment and the relevance of clinical management between the two. PSCI is a common and serious complication after stroke, with a high incidence, which seriously affects the quality of life and prognosis of patients. In addition, the survival time of patients is significantly reduced, and it can increase the risk of recurrent stroke, thereby placing a heavy burden on society and families [5]. The current treatments for PSCI are oral acetylcholinesterase inhibitors, anti-glutamate drugs, antioxidants, non-steroidal anti-inflammatory agents, and hormone replacement therapies. Recent studies have shown that the anticholinergic function of such drugs has certain limitations and can have a certain effect on patients’ memory [6, 7]. The treatment of PSCI with oral drugs alone is not ideal and has obvious side effects.

Acupuncture, as an important part of the appropriate technology of traditional Chinese medicine (TCM), is currently the most commonly used complementary and alternative treatment [8].. Acupuncture has a significant regulating effect on human psychology. Modern studies have found that acupuncture can improve cognitive function by affecting cerebral blood flow and hemorheology, protecting the internal structure of brain nerve cells [9]. The theory of TCM holds that acupuncture can regulate the balance of Qi and blood in the human body, it can improve human function. Acupuncture is becoming more and more popular with clinicians and patients for its unique advantages of simplicity, low cost, and significant efficacy. Based on the current needs of patients with PSCI who have poor response to conventional treatment and obvious adverse reactions, as well as the need for clinical research on the level of evidence for this effect, it is worthwhile to further explore the treatment model of acupuncture for PSCI. Therefore, we will evaluate the clinical effectiveness and safety of acupuncture in the treatment of PSCI. In this manuscript, we describe the rationale and the detailed methodology of the trial. This protocol is guided by the Standard Protocol Items: Recommendations for Interventional Trials (SPIRIT) (Fig. 1 and Additional file 1: Table S1).

**Fig. 1 Fig1:**
[figure not shown]
SPIRIT figure for the schedule of enrollment, interventions, and assessments. Abbreviations*: MOCA* Montreal Cognitive Assessment Scale, *MBI* Modified Barthel Index Rating Scale, *MMSE* Mini Mental State Examination Scale, *CDR* Clinical Dementia Rating Scale, *NPI* Neuropsychiatric Inventory, *SS-QOL* Stroke-specific quality of life scale, *SPIRIT* Standard Protocol Items: Recommendations for Interventional Trials, *TCM* traditional Chinese medicine

### Randomization and blinding

The attending physician will determine eligible patients based on the inclusion and exclusion criteria. The attending physician will obtain informed consent and refer participants to the study coordinator, who will randomly assign them to the intervention or control department. The research coordinator will keep a random list generated in advance by a biostatistician using a computerized random number generator and will assign treatment plans accordingly. The attending physician who will recruit participants will not understand the order of allocation. The biostatistician and research coordinator will keep the random list until the end of the research to ensure that the assignment is hidden. Therefore, the data analyst will be unaware of the allocation. Participants will be instructed not to disclose the allocation to the attending physician.

### Control group

#### Basic treatment of stroke

Refer to “Guidelines for the Prevention and Treatment of Cerebrovascular Diseases in China” (Department of Disease Control, Ministry of Health, Neurological Society of Chinese Medical Association, 2005. Control blood pressure, use individualized treatment to stabilize blood pressure below 135/85 mmHg or within normal range, select appropriate blood glucose hypoglycemic drugs, control blood sugar within the normal range, select lipid-lowering drugs according to triglyceride and cholesterol, antiplatelet aggregation, symptomatic treatment, prevention, and treatment of complications). A question that needs to be highlighted: regarding the application of antiplatelet drugs, we will apply them according to clinical practice. For patients with ischemic stroke, we will give antiplatelet aggregation drugs. For patients with hemorrhagic stroke, we will not give antiplatelet drugs.

Patients will be given corresponding symptomatic drugs (control of blood pressure, blood sugar, etc.) and regular rehabilitation training (sitting balance training, standing balance training, transfer training, walking training, occupational therapy, etc.). According to the different results of each patient’s cognitive function assessment, take corresponding, one-to-one cognitive function training, including (1) memory training back number, back number, short text retelling, word pairing, etc., and guide patients to use association memory techniques such as methods, segmentation methods and story-writing methods to improve memory effects and guide patients to use their own auxiliary equipment, such as notebooks, cards, and electronic notebooks to assist in the completion of daily affairs; (2) attention training visual tracking, guessing games, computer games, etc.; (3) computational training: designing some content related to daily life for patients to perform calculations, such as simulating shopping and grocery shopping in supermarkets; (4) arrangement and daily routines for execution and problem-solving life-related problems for patients to solve, such as cakes and dressing; (5) apraxia, agnosia training, various sensory stimulation of the affected limb, standing on the affected side, speaking to the patient, etc. The patient repeatedly trains to identify items, shapes, colors, etc. and makes full use of other sensory stimuli such as tactile sensation and hearing. For patients with apraxia, the various movements of daily life are decomposed and practiced, and then continuous movements are trained, and the patients are guided by hand to carry out activities. For patients with mental and motor apraxia, use verbal guidance and use their subconscious movements. Cognitive considerations: (1) avoid analgesics as much as possible during the training of cognitive impairment; (2) create a stimulating atmosphere as much as possible, often give the patient a certain stimulus, let the patient touch the environment, and even consider the position of the bed, should be placed in a prominent position, the patient should not be isolated in the ward; and (3) the patient’s psychological barriers should be lifted. In addition to cognitive problems, patients with cognitive impairment may also have different psychological conditions, such as depression and depression. Only by lifting these psychological barriers can the interest of the patients be stimulated and the confidence of the patients can be improved.

### Intervention group

In this group of patients, we will give the same treatment as the control group. At the same time, on this basis we will give acupuncture treatment. (1) Head acupuncture treatment. Acupoint selection: *Baihui, Sishencong, Shenting,* and *Benshen*, with mental behavior symptoms, plus *Neiguan and Shenmen*. Refer to the sixth edition of acupuncture for acupoint positioning. Operation method: generally take a sitting position, depending on the condition, you can also use the supine or lateral position, using Huatuo brand 0.30 mm diameter, 25-mm-long needle (Suzhou Medical Supplies Factory Co., Ltd.). The needle is about 30° from the scalp, twist the needle diagonally along the selected acupuncture point, the depth of the acupuncture is suitable to reach under the cap-shaped aponeurosis, and twist continuously for 2–3 min quickly, and then connect GM-101 type acupuncture instrument, continuous wave, tolerated by the patient as a degree, changed to sparse and dense wave after 15 min. Remove electroacupuncture after 30 min and continue to retain the needle for 1 h; during needle retention, twist the needle every 30 min. Once a day, five times a week for 4 weeks. (2) Moxibustion treatment. Acupoint selection: *Shenting, Baihui, Shendao, Fengfu, Xinyu,* and *Ganshu*. Operation: use mild moxibustion. First, assist the patient to take the prone position, fully expose the moxibustion site, and then place the moxa stick into the moxibustion device head, aim at the acupoints of Shenting, Baihui, Shinto, Fengfu, Xinyu, and Ganshu, wait for the local skin to be red, have a warm and comfortable feeling, last for 30 min. Adjust the height of the moxibustion head in time according to the patient’s feelings, observe the patient’s local skin color, and avoid blisters caused by excessive temperature, five times/week for 4 weeks.

We will use sterile disposable stainless steel needles of 0.25 mm diameter, 25 mm or 40 mm long and 0.30 mm diameter, 50 mm or 70 mm long, depending on the acupuncture points. In addition to the main acupuncture points specific for the treatment of PS CI, the TCM physicians will be allowed to make minor adjustments to the acupuncture points in view of the differing constitution of the patients as per the holistic treatment philosophy of TCM. Therefore, the number of needles to be inserted per subject per session will differ. The needles will be inserted from 0.25 to 1 in. deep depending on the acupuncture points. After eliciting the de qi response, the needles will be left in place for 30 min. The needles will be stimulated manually every 10 min. The acupuncture treatment will consist of a total of 10 sessions (or 2 courses) in total. Each course of treatment will consist of 5 acupuncture sessions held over 2 weeks, each session lasting 30 min. The patient will have a break of at least 3 days and up to 1 week in between each course of acupuncture. TCM physicians will document components of treatment and adherence in standardized logbooks.

The anatomical location of each acupuncture point is as follows: Baihui is located in the middle of the top of the head, in the cap-shaped aponeurosis; around it, there are left and right superficial temporal arteries and veins anastomotic network, as well as the branches of the greater occipital nerve and the frontal nerve. Sishenchong is also located in the galea aponeurosis; it is surrounded by occipital arteries, veins, superficial temporal arteries, venous top branches and supraorbital arterial and venous anastomotic nets, great occipital nerve, auricular cervical nerve, and supraorbital nerve branches. Shenting is located at the junction of the left and right frontal muscles; it is surrounded by frontal arteries and veins, as well as frontal nerve branches. Benshen is in the frontal muscle; it is surrounded by supraorbital arteries, veins, supraorbital nerves, and superficial temporal arteries and veins. Neiguan is located between the palmar longus tendon and the flexor carpi radialis tendon. Its deep part is the pronator; it is surrounded by the median forearm vein, the median artery, the anterior arteries and veins between the bones, and the inner and outer cutaneous nerves of the forearm. There are median nerve trunk and anterior interosseous nerve distribution. Shenmen is located between the flexor carpi ulnaris and the superficial digita flexor muscles, and the deep layer is the deep digita flexor; underneath it is the ulnar artery passing through; it is surrounded by the medial forearm cutaneous nerve.

### Primary outcomes

The selection of outcomes will be evaluated by Mini Mental State Examination Scale (MMSE) [10]. This scale will be conducted by two trained assessors who performed a combined MMSE examination of the patient, using conversation and observation. After the MMSE test would have been over, the two raters independently will score and take the average of the two as the final score. According to the international agreement MMSE score, the scale will include the following 7 aspects: time-oriented force, place-oriented force, immediate memory, attention and computing power, delayed memory, language, and spatial perception. A total of 30 items, each answer is worth 1 point, the answer is wrong or do not know the answer 0 points, the total scale of the scale is 0–30 points. The test results will be closely related to cultural level. Scoring reference: scores 27–30 are normal, scores < 27 can be considered cognitive impairment, scores 21–26 are mild cognitive dysfunction, scores 10–20 are moderate cognitive dysfunction, and a score of 0–9 is considered severe cognitive impairment. The primary and secondary outcome measures are shown in Table 1.

**Table 1 Tab1:** Treatment schedule and outcome measures

Items	Before treatment	Treatment period, twice a week, 8 times in total (treatment starts within 1 week after registration)				Post observation period
Time point	Registration	Week 1–4	Week 6	Week 8	Week 12	2 weeks later treatment completion
Inclusion criteria	√					
Exclusion criteria	√					
Informed consent	√					
Confirmation of subjective symptoms	√	√	√	√	√	√
Mini Mental State Examination Scale	√		√		√	√
Traditional Chinese Medicine Syndrome Score	√		√		√	√
Observation of adverse events		√	√	√	√	√

### Secondary outcomes

For the secondary outcomes, we will use the Montreal Cognitive Assessment Scale (MOCA) [11]. It is an assessment tool for rapid screening of cognitive abnormalities. It includes 11 inspection items in 8 cognitive areas including attention and concentration, executive function, memory, language, visual structure skills, abstract thinking, computing, and orientation. The total score is 30 points and ≥ 26 points are normal. It has high sensitivity, covers important cognitive areas, and has a short test time, which is suitable for clinical application. However, it is also affected by education level, differences in cultural background, the examiner’s skills and experience in using MoCA, the environment of the examination, and the emotional and mental state of the testee will all affect the score, and for mild cognitive function, obstacles are more sensitive, as education level will be considered to be the most independent factor affecting the MOCA score. In order to correct the bias caused by education level, the total score is increased by 1 point for subjects with less than 12 years of education. For subjects with 4–9 years of education, the total score is increased by 2 points, and for those with 10–12 years of education, the score is increased by 1 point. This can better correct the bias caused by low education levels.

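### The MoCA education correction is given as two rules that yield different scores, and Table 1, said to show the secondary outcomes, has no MoCA row

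*Protocol article*

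**What the plan says.** All references are to the protocol article.

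- **Secondary outcomes, the measure.** The section opens "For the secondary outcomes, we will use the Montreal Cognitive Assessment Scale (MOCA" and names no other measure. It describes the scale as follows: "The total score is 30 points and ≥ 26 points are normal".
- **Secondary outcomes, the correction.** To offset the effect of schooling, "the total score is increased by 1 point for subjects with less than 12 years of education". The next sentence reads "For subjects with 4–9 years of education, the total score is increased by 2 points", and continues "for those with 10–12 years of education, the score is increased by 1 point". The aim is then given: "This can better correct the bias caused by low education levels".
- **Primary outcomes, the table.** The section ends "The primary and secondary outcome measures are shown in Table 1". The table is titled "Treatment schedule and outcome measures". Its only scale rows are the MMSE and the TCM syndrome score.

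**The concern.** The two correction sentences stand next to each other, and each looks complete. The first has one threshold; the second has two bands. No wording links them, so a rater cannot tell which to apply or whether to apply both. The bands also start at 4 years, while the Inclusion/exclusion criteria set no minimum of schooling, so patients with 0–3 years can enter the trial.

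What is at stake is the scoring of the only measure named as a secondary outcome. The Instruments and definitions section gives MoCA some weight: it says the MMSE has a ceiling effect and poor sensitivity to mild impairment and needs other scales beside it, and then describes MoCA. The Secondary outcomes section itself treats education as the leading independent influence on the MoCA score.

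The table raises a second question. The text sends the reader to Table 1 for the secondary outcomes, and the one named secondary outcome is not there.

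**Working it through.** **Inputs.** First rule: +1 below 12 years. Bands: +2 for 4–9 years, +1 for 10–12 years. Normal limit: 26 of 30. All come from Secondary outcomes. The article gives no worked score to reproduce.

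**Step 1. Points added under each reading.**

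| Years of education | First rule alone | Bands alone | Bands override first rule | Both added |
|---|---|---|---|---|
| 0–3 | 1 | 0 | 1 | 1 |
| 4–9 | 1 | 2 | 2 | 3 |
| 10–11 | 1 | 1 | 1 | 2 |
| 12 | 0 | 1 | 1 | 1 |
| 13 or more | 0 | 0 | 0 | 0 |

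Taken alone, the two rules differ by 1 point at 0–3, 4–9 and 12 years, and agree only at 10–11 and at 13 or more. Across all four readings the widest spread is at 4–9 years: 3 − 1 = 2 points.

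**Step 2. Direction of the correction.** With the bands alone, 3 years of schooling earns 0 and 4 years earns 2. If the bands override, 0–3 years earns 1 against 2 at 4–9 years. If both are added, it earns 1 against 3. In these three readings the group with least schooling is corrected less than the next group up. Under the first rule alone, everyone below 12 years earns the same 1 point.

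**Step 3. Effect on classification.** Corrected score = raw score + points. For 5 years of schooling and a raw score of 24:

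- first rule: 24 + 1 = 25, below normal;
- bands alone, or overriding: 24 + 2 = 26, normal;
- both added: 24 + 3 = 27, normal.

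Equivalently, the raw score needed to be classed as normal at 4–9 years is 26 − 1 = 25, 26 − 2 = 24 or 26 − 3 = 23.

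**Step 4. Effect on change and on the comparison of arms.** Let c be a patient's correction. It depends on schooling only, so under one rule it is the same at every visit, and (follow-up + c) − (baseline + c) = follow-up − baseline. This assumes no cap on the corrected total; the article mentions none. In a comparison of follow-up scores, c has the same expected value in both arms by randomisation. It then alters the spread between patients but does not bias the difference between arms.

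**Step 5. Table 1 against the outcome text.**

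| Measure | Outcome sections | Table 1 |
|---|---|---|
| MMSE | Primary | Registration, week 6, week 12, 2 weeks after completion |
| MoCA | Secondary, the only one named | No row |
| TCM syndrome score | Not declared | Same four time points as MMSE |

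The readable text gives no MoCA time point. The legend of Fig. 1, the schedule figure, lists MoCA among its abbreviations; the figure itself is not available here.

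**The case against.** The strongest reply is that little follows from the conflict. Education is fixed, so any rule applied consistently drops out of change from baseline, and randomisation balances it between arms. The 26-point limit describes the instrument: no stated endpoint or eligibility rule uses it, and eligibility rests on MMSE below 27. The primary outcome is not involved. All of this stands, and it limits the size of the point.

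Three stronger readings are tempting, and the article does not support them.

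- **That the least educated always get the smallest correction.** With the bands overriding, 0–3 years ties with 10–12 years. With both added, it ties with 12 years. With the bands alone, it ties at zero with 13 or more. Under the first rule alone there is no gradient. What holds is the comparison with 4–9 years in three of the four readings.
- **That the ambiguity creates false change or a biased treatment effect.** This needs one patient scored under different rules at different visits. The wording does not prevent it, but nothing suggests it is planned.
- **That MoCA will not be collected.** Fig. 1 may schedule it. The omission from Table 1 is an inconsistency and not proof that MoCA is unscheduled.

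It can also be said that a listing in Table 1 is itself a declaration of the TCM score. That is arguable, since the text says the table shows the outcomes. But the same argument would leave MoCA undeclared, so the text and table need reconciling either way.

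Finally, the choice of covariates is commonly left to the analysis plan. That is fair: its absence here is no defect, and adjustment is offered below only as the way to make the result independent of the correction.

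**Conclusion.** The point holds for the scoring rule and for the mismatch with Table 1. As written, the correction cannot be followed in one way. The two rules differ by 1 point at 0–3, 4–9 and 12 years, and the readings differ by up to 2 points at 4–9 years if the rules are added. Absolute MoCA scores and any classification at 26 depend on the choice. Change scores under one consistent rule, the unbiasedness of the comparison between arms, and the primary MMSE outcome do not.

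How many patients are affected cannot be said, because the article gives no distribution of schooling. The conclusion takes the sentences at face value; they are intact running prose, so damage in reading the PDF is unlikely. This is a correction the sponsor should make, but it does not threaten the trial's main result.

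**What to change.** 1. State one education correction that covers every level of schooling, including 0–3 years and exactly 12 years, with no gap and no reversal. Delete the other.
2. Record the raw MoCA total and years of education on the CRF. The Trial status section says the study is under way; with both items on file, any patient can be rescored under the final rule.
3. Compare the arms on raw MoCA, adjusted for baseline MoCA and years of education, so that the result does not depend on the correction. Keep the corrected score for any classification at 26.
4. Add MoCA to Table 1 at its intended time points, consistent with Fig. 1, and state whether the TCM syndrome score is a secondary outcome or exploratory.

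The cost is wording in the protocol, Table 1 and the CRF, and a small change to the MoCA analysis, since the Statistical analysis section now lists t tests, rank sum tests and analyses of variance. No new assessment or extra patient is needed.
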